## Abstract

**Objectives:**

The primary aim is to compare the effects of backward walking exercise to forward walking exercise on knee pain, knee functions, and thigh muscle strength in individuals with mild to moderate knee osteoarthritis using lower body positive pressure, in addition to mobility functions, balance, and self-reported health status.

**Methods:**

The study is a single blind randomized clinical trial with two independent groups. This study will enroll 26 participants with mild to moderate knee osteoarthritis. The participants will be randomized into either experimental group (backward walking exercise) or control group (forward walking exercise). Both groups will use lower body positive pressure treadmill for walking exercise. Both groups will perform regular conventional exercise and worm-up exercise before walking exercise. The treatment will be three times a week for six weeks. Walking session will be up to 30 min each session. Data collection will be collected during pre- and post- intervention including primary outcomes including numeric pain rating scale (NPRS), knee injury and osteoarthritis outcome score (KOOS), and thigh muscle strength test. The secondary outcomes include five times sit to stand test (FTSTS), 3-meter backward walk test (3MBWT), timed up and go test (TUG), four square step test (FSST), functional reach test (FRT), 10-meter walk test (10-MWT), six minute walk test (6MWT), medical outcomes study short form 12 (SF-12), patient health questionnaire -9 (PHQ-9), and rapid assessment of physical activity (RAPA). An independent t-test will be used to evaluate the effect of treatment on the outcome measures.

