##### Numeric pain rating scale (NPRS)

The 11-point NPRS measures pain severity from 0 to 10, where 0 indicates "no pain" and 10 indicates "worst imaginable pain." The NPRS has excellent internal consistency (Coefficient alpha = 0.84) [19] and has been validated to evaluate pain severity [20]. Minimal clinically important difference (MCID) in individuals with osteoarthritis is from 1 to 1.7 points or a change of 15–27.9% [21, 22]. At baseline, participants will rate their pain over the past 24 h using the NPRS. The NPRS will be taken before each session, throughout gait training, and after six weeks.

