##### Knee injury and osteoarthritis outcome score (KOOS)

The KOOS assesses knee pain, symptoms, and level of disability during the last week [23]. It has five subscales: Pain; Symptoms; Function in ADLs; Sports and Recreation; and Quality of Life. Each subscale has a normalized score from 0 to 100, where 0 represents extreme symptoms and 100 represents no symptoms. The test is valid, reliable, and responsive to change for people with knee OA [24]. The minimal detectable change (MDC) is from 8 to 10 points [25]. A validated Arabic version of KOOS will be utilized for this study [26].

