##### Knee flexor and extensor muscles strength

An isokinetic dynamometer (Biodex Model 4Pro, N.Y. 11,967, U.S.A) will be used to assess isometric knee flexion and extension strength of both sides [27]. The hip angle will be at 85° of hip flexion and the knee angle will be at 60° of knee flexion [28]. Both legs will be tested, and the trial order will be randomized. Patients will be instructed to exert as much effort as they could for five seconds during each test. We will explain the test procedure to the participants and provide 5 min warm-up cycling before the test. To avoid fatigue, 60-s rest time between trials will be provided. The testing session will be directed by the same investigator, who will verbally encourage each participant to perform their best. The peak torque obtained over the 3 repetitions will be recorded. Peak torque measurement is considered the most valid method to assess the muscle strength in individuals with knee OA [29].

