### Statistical analysis

The collected data will be analyzed with IBM SPSS version 28.0 (IBM Corp., Armonk, NY, USA). The descriptive demographic data (means, medians, standard deviation, and frequencies) include age, gender, onset of knee OA, height, weight, knee involved, and all primary and secondary outcome measures will be computed and compared between two groups at the baseline using independent t-test. The Shapiro–Wilk test will be used to evaluate the normality assumption. A dependent *t*-test or Wilcoxon signed rank test will be performed to evaluates the difference between pre-intervention and post-intervention. The independent *t*-test or Mann–Whitney *U*-test will be performed to evaluate the difference between groups at the baseline and post-intervention. The level of significance will be set at *p* < 0.05.

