### Future directions and clinical implications

We have proposed a study protocol where knee pain in people diagnosed with OA is treated conservatively by walking exercise using LBPP. The primary goal of the study is to assess whether backward walking exercise using LBPP can alleviate knee pain symptoms in individuals diagnosed with OA. We believe that specific combinations of using a LBPP treadmill and doing backward exercises will relieve knee pain. As such, conservative treatment might be more cost-effective and have better outcomes than other treatments, such as surgical procedures.

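### Three unranked primary instruments give about eight primary tests, each at an unadjusted 0.05, with no rule for what counts as a positive primary result

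*Protocol article*

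**What the plan says.** The Abstract (Methods) lists "primary outcomes including numeric pain rating scale (NPRS), knee injury and osteoarthritis outcome score (KOOS), and thigh muscle strength test". The Objectives likewise state the primary aim jointly, as an effect "on knee pain, knee functions, and thigh muscle strength in individuals with mild to moderate knee osteoarthritis". Neither place ranks the three.

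Two of the three instruments yield several scores. For KOOS, "It has five subscales: Pain; Symptoms; Function in ADLs; Sports and Recreation; and Quality of Life", and "Each subscale has a normalized score from 0 to 100"; no total score and no lead subscale is named. For strength, the dynamometer "will be used to assess isometric knee flexion and extension strength of both sides". Under Inclusion criteria, the most symptomatic knee is the one that enters the outcomes when osteoarthritis is bilateral.

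Study design schedules all outcome measures at baseline (T0) and after six weeks (T1). Statistical analysis compares groups by independent t-test or Mann–Whitney U-test at those two times. One threshold serves every test: "The level of significance will be set at" p < 0.05. There is no order of testing, no correction, and no statement of how many primary outcomes must succeed.

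Two other sections point to pain alone. Sample size calculation rests on pain level changes from a prior study. Future directions and clinical implications says: "The primary goal of the study is to assess whether backward walking exercise using LBPP can alleviate knee pain symptoms".

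**The concern.** A 5% significance level limits the false-positive risk of one test. When several outcomes share primary status and nothing says how they combine, the trial's main claim has no defined error rate. A single significant KOOS subscale or muscle group could then be presented as a positive primary result, with nothing in the plan to rule that out.

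This matters here because there are only 13 participants per arm (11 after the planned attrition), so one isolated significant score is a plausible chance event. The document also disagrees with itself: the primary list covers pain, function and strength, while the sizing and the stated primary goal concern pain only.

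**Working it through.** The document states no family-wise error rate, so there is no figure of its own to reproduce.

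**Inputs**
- NPRS at T1: 1 score.
- KOOS: 5 subscale scores (KOOS section).
- Strength: flexion and extension, 2 scores if only the index knee counts (Inclusion criteria) or 4 if both legs count (strength section).
- Level per test: 0.05 (Statistical analysis), assumed two-sided because sidedness is not stated.
- Group size: 11 or 13 per arm (Sample size calculation).
- Correlation between outcomes: not given; a common value of 0.3 to 0.7 is assumed.
- Success rule: not given; the calculation assumes that any one significant result may be reported as a primary finding.

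**Count.** Index knee only: 1 + 5 + 2 = 8. Both legs: 1 + 5 + 4 = 10. One test per instrument: 3.

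**Independent outcomes, false difference in either direction:** 1 − 0.95^k.
- k = 8: 1 − 0.663 = 0.337
- k = 10: 1 − 0.599 = 0.401
- k = 3: 1 − 0.857 = 0.143

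**Independent outcomes, false result favouring backward walking:** 1 − 0.975^k, because a two-sided 0.05 test leaves 0.025 in each direction.
- k = 8: 1 − 0.817 = 0.183
- k = 10: 1 − 0.776 = 0.224
- k = 1: 0.025

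**Correlated outcomes.** Two-sample t-tests were simulated with no true difference and a common correlation among outcomes. Results at 11 and 13 per arm agree closely.

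| Tests | Direction | Correlation 0.3 | 0.5 | 0.7 |
|---|---|---|---|---|
| 8 | either | 30–31% | 26% | 19–20% |
| 8 | favouring backward walking | 15–16% | 13% | 10% |
| 10 | either | 35–36% | 29–30% | 22% |
| 3 | either | 14% | 13% | 11% |

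At a correlation of 0.9, eight tests still give about 12% in either direction. With block correlations (0.6 to 0.7 among the patient-reported scores, 0.7 to 0.8 between the strength scores, 0.2 to 0.3 across the two groups of scores), eight tests give 23 to 26%.

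**After the fix.** One named primary test has a 5% error rate. Holm over three tests, with the smallest p-value compared against 0.05/3 = 0.0167, holds the family-wise rate at or below 5% whatever the correlation.

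**The case against.** Several parts of the opposing case stand.

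- **Both legs.** A reader might take the two-sided strength measurement to mean 10 primary tests and an error rate of 40%. The strength section says which legs are measured, not which enter the primary analysis, and the index-knee rule favours eight. Ten tests is an upper case, and 40% is its ceiling under independence.
- **The any-hit rule.** A reader might say that the plan counts any significant subscale, leg or muscle group as success. It does not say so. If every primary had to succeed, the family-wise error would not be inflated. The defect is that the rule is left open.
- **Direction.** The Introduction hypothesises a benefit of backward walking. The 19 to 34% range counts false differences either way; a false result favouring backward walking runs at about half that.
- **In-session pain scores.** The NPRS section says "The NPRS will be taken before each session, throughout gait training, and after six weeks". A reader might infer further primary tests, or that the chamber pressure is adjusted to the NPRS score. Neither is supported: Study design and Statistical analysis confine outcomes and between-group tests to T0 and T1, and the Intervention section does not say that the NPRS score sets the pressure.
- **Pain is not the same as NPRS.** The sizing and the stated goal refer to pain without naming NPRS, and KOOS has its own Pain subscale. Choosing NPRS is consistent with the text, not dictated by it.

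It can also be said that an analysis plan, not shown, may hold a correction. A missing correction alone would be no finding. But the article itself fixes three unranked primaries and one threshold, and it gives conflicting signals about which outcome leads.

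**Conclusion.** The concern holds: the protocol fixes several primary outcomes at an unadjusted 0.05 without ranking them or defining a positive result.

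With index-knee strength there are about eight primary tests. If any one may be reported as a primary finding, the chance of at least one false primary difference in either direction is about 34% under independence and about 19 to 31% at assumed correlations of 0.7 to 0.3. For false results favouring backward walking it is about 10 to 18%, against 2.5% for one test. Even one test per instrument gives 11 to 14% in either direction, so the conclusion does not depend on how KOOS and strength are split.

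These sizes rest on three assumptions that the document does not settle: two-sided testing, the any-hit rule and the correlations. Correlations above 0.7 would lower the rates, though not to 5%. The planned pre-to-post tests within each group are not counted.

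**What to change.** Make the choice before any outcome data are seen. Either option below resolves the point.

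1. **One primary outcome.** Name NPRS at T1, compared between groups, which is consistent with the sample size section and the stated goal. Make KOOS and index-knee strength secondary, reported with estimates and confidence intervals.
2. **Three primaries with control.** Keep NPRS, one named KOOS subscale and one named index-knee strength measure, tested with Holm across the three.

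Under either option, state that only the index knee enters the strength comparison, so that the Inclusion criteria and strength sections agree.

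The cost is wording in the protocol and analysis section, plus a registry update. Treatment, visits and measurements do not change. Option 1 takes primary status from KOOS and strength, so the jointly stated primary aim must also be rewritten. Option 2 keeps all three domains but loses some power per outcome, which matters with 11 to 13 per arm.

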**Results:**

Not applicable.

**Conclusion:**

Using lower body positive pressure may have promising results against knee osteoarthritis. Moreover, walking backward exercise using lower body positive pressure might add more benefits to individuals with knee osteoarthritis and help clinicians in decision making.

*Trial registration*: This study was registered in ClinicalTrails.gov (ID: NCT05585099).

## Introduction

Osteoarthritis (OA) is a joint degenerative disease affecting more often adults aged 65 year and older [1]. Globally, the pooled prevalence on knee OA was 16% in people aged 15 and older and 22.9% in those aged 40 and older [2]. Knee OA is the most common arthritis [3] that causes disability and interferes with activities of daily life (ADLs) [4], and quality of life [5], and increases the risk of fall [6]. Several symptoms are associated with knee OA including pain, stiffness, knee muscle weakness, compromised joint integrity, poor balance, and limited knee range of motion [7, 8]. However, non-surgical interventions such as physical therapy, exercise, and manual therapy along with patient education are important and often efficacious for improving patient-related outcomes in individuals with knee OA [9, 10].

Walking exercise is an effective and recommended treatment for individuals with knee OA in minimizing pain and disability [11]. Likewise, backward walking exercise was efficacious in reducing knee OA symptoms than forward walking exercise [12]. Backward running also reduces compressive stresses at the patella-femoral joint, compared with forward running [13], which may alleviate knee pain and improve knee function. Backward walking training have been reported to increase quadriceps muscle strength in individuals with knee OA [12, 14].

Adding backward walking exercise to a traditional treatment program for three weeks improved function and decreased disability in individuals with knee OA [15]. Furthermore, six weeks of backward walking exercise resulted in a higher decline in pain and functional disability compared to forward walking exercise and control groups which receive conventional physical therapy, as well as improved quadriceps muscle strength and performance [12]. However, there was no significant difference between forward walking and backward walking exercise in all outcome measures. Furthermore, forward walking exercise and backward walking exercise were on overground which may increase the force on the knee due to the body weight loading and limit the exercise duration which was 10 min.

Lower body positive pressure (LBPP) treadmill uses air pressure chamber to unload body weight during walking or running [16]. Reducing compressive forces at knee joint by decreasing body weight while walking or running often recommended to patients with knee OA [17]. Using LBPP for walking exercise stimulated weight loss and reduced knee pain [17]. LBPP has been shown to decrease knee pain in individuals with knee OA [17]. Compared to regular treadmills [18] in forward walking exercise, potentially by reducing the compressive forces at the knee joint while walking. However, previous studies only investigate forwarding walking exercise in LBPP. The advantages of backward walking exercise using LBPP have not been investigated yet. Thus, this randomized controlled trial (RCT) aims to investigate the effects of backward walking exercise using LBPP compared to forward walking on knee pain and functions in individuals with mild to moderate knee OA. We hypothesized that backward walking exercise could provide additional benefits to knee symptoms and functions more than forward walking exercise using LBPP. A secondary aim is to examine the effects of backward training compared to forward training on mobility functions, balance, and self-reported health status in this population.

## Materials and methods

### Study design

This study is a prospective two-arm single-blinded RCT. The experimental group (EG) will perform backward walking exercise, and the control group (CG) will perform forward walking exercise using LBPP device. All outcome measures will be collected at baseline (T0) and post-intervention following 6 weeks or 18th session (T1) (Fig. 1).

**Fig. 1 Fig1:**
[figure not shown]
Flow diagram of study protocol

### Ethical approval

All procedures and intervention will be carried out in compliance with the 1964 Helsinki Declaration and its later amendments or comparable ethical standards, as well as the ethical standards of the institutional research committee. The ethical approval from National Bioethics Committee Review Boards of Qassim University was obtained before the start of the study (protocol number 22-07-07). In addition, this study was prospectively registered in ClinicalTrails.gov (18/10/2022; ID: NCT05585099).

### Participants and recruitment

A sample consisting of 26 men and women with knee OA is required to be allocated to each group (*n* = 13 per group). The participants will be recruited from surrounding communities. All participants will read and sign an informed consent form that describes the study protocol, risks, and benefits. Figure 2 depicts the study’s expected timeline for enrollment, evaluation, and treatment. All data collection and intervention will take place at the Qassim University Medical City's physical therapy department in Saudi Arabia.

**Fig. 2 Fig2:**
[figure not shown]
Standard protocol items: recommendations for content for the schedule of enrollment, interventions, and assessments for interventional trials (SPIRIT) checklist, (EG) experimental group, (CG) control group, (NPRS) numeric pain rating scale, (KOOS) knee injury and osteoarthritis outcome score, (TMS) thigh muscle strength test, (FTSTS) five times sit to stand test, (3MWB) 3-meter walk backward test, (TUG) timed up and go, (FSST) four square step test, (FRT) functional reach test, (10-MWT) 10-meter walk test, (6MWT) 6-minute walk test, (SF-36) short form 36, (PHQ-9) Patient Health Questionnaire-9, (RAPA) rapid assessment of physical activity

### Inclusion criteria

Participants should: (1) be ≥ 40 years old; (2) have been diagnosed with a mild to moderate knee OA by a physician and confirmed by radiograph imaging (Kellgren & Lawrence grade 1–3); (3) complain of knee pain during the past 30 days; (4) and have unilateral or bilateral knee OA. To determine knee OA diagnosis, the X-ray will be obtained from standing position using anteroposterior images. If the patient has bilateral knee OA, the most symptomatic knee indicated by the patient will be included in the outcomes.

### Exclusion criteria

Participants will be excluded if they: (1) have a history of ankle, knee, or hip injury or medical operation within the past 12 months; (2) are diagnosed with rheumatoid arthritis; (3) have used knee injection for their knee OA pain within the past year; (4) have a history of other medical conditions that would interfere with walking; (5) received physical therapy during the past 3 months for their knee OA; (6) and are pregnant.

### Outcome measures

#### Primary outcome measures procedures

##### Demographic and clinical variables

Demographic information pertaining to patient’s age, sex, and education level will be collected. Clinical variables include OA diagnosis type and severity, having other chronic conditions (e.g., diabetes mellitus and high blood pressure), prescribed medications, history of falls during the last 12 months, average pain level in the past month, body measures [height, weight, and body mass index (BMI)], and physical activity (minutes per week) will be obtained.

##### Numeric pain rating scale (NPRS)

The 11-point NPRS measures pain severity from 0 to 10, where 0 indicates "no pain" and 10 indicates "worst imaginable pain." The NPRS has excellent internal consistency (Coefficient alpha = 0.84) [19] and has been validated to evaluate pain severity [20]. Minimal clinically important difference (MCID) in individuals with osteoarthritis is from 1 to 1.7 points or a change of 15–27.9% [21, 22]. At baseline, participants will rate their pain over the past 24 h using the NPRS. The NPRS will be taken before each session, throughout gait training, and after six weeks.

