##### Intervention

After signing the informed consent form, participants will fill out an intake form about demographic data and clinical variables. Additionally, they will be evaluated on inclusion/exclusion criteria. Participants meeting the inclusion criteria will be recruited in the study and assessed on the primary and secondary outcome measures. For test order, participants will be randomly assigned to one of four groups. A counterbalanced approach will be used to manage the order effects of learning and fatigue associated with the administered tests.

Participants will be randomized on the first day of the intervention to either a EG or CG. All participants will receive manual therapy and therapeutic exercise (Table 1) as described previously [12]. LBPP (AlterG Anti-Gravity Treadmill, Fremont, CA, USA) will be used for both forward and backward walking exercise (Fig. 3). All participants will have three sessions a week for 6 weeks (18 sessions) for up to 1 h/session. For the CG, gait training will be trained on forward walking using LBPP. The EG will be trained on backward walking using LBPP. For both groups, progression of gait training time will be instructed to gradually increase up to 30 min over the 6 weeks period. The air pressure inside chamber will be set to achieve pain free or max pain relief. Treadmill speed will be continuously assessed and increased gradually depending on the patient’s capacity. All participants will have 5 min of warm-up and cool-down exercise including heel raise, and hamstring and gastrocnemius-soleus stretches. All interventions and activities will be formed with a supervision of licensed physical therapists. Physical therapists will be trained on delivering the intervention and reporting the needed data each session. Before beginning the study, the evaluator will receive training on data collection and measuring all outcome measures.

**Table 1 Tab1:** Protocol exercise for all groups

Exercise	Procedure	Frequency	Intensity	Progression
Isometric quadriceps exercise	Patients lay in a supine position. A rolled-up towel was put beneath the knee. They were instructed to maximally activate their thigh muscles in order to straighten their knee and hold the contraction for 5 s	3 days/week	1 set of 10 repetitions/twice a day	1st week: 1 set 2–3 weeks: 2 sets 3–6 weeks: 3 sets

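### The arm comparison on pain uses one unadjusted post-intervention NPRS score, ignoring the baseline score and the session ratings of anyone who drops out

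*Protocol article*

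**What the plan says.** The NPRS section, under the primary outcomes, states: "At baseline, participants will rate their pain over the past 24 h using the NPRS". It then adds: "The NPRS will be taken before each session, throughout gait training, and after six weeks". The Intervention section fixes the number of sessions: "All participants will have three sessions a week for 6 weeks (18 sessions").

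The Study design section names two outcome times: "All outcome measures will be collected at baseline (T0) and post-intervention following 6 weeks or 18th session (T1").

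For the comparison of arms, the abstract states: "An independent t-test will be used to evaluate the effect of treatment on the outcome measures". The Statistical analysis section says the independent t-test or Mann-Whitney test "will be performed to evaluate the difference between groups at the baseline and post-intervention". Paired tests are reserved for "the difference between pre-intervention and post-intervention", which is a within-group question. No stated analysis uses a rating taken at a session, and no stated comparison of arms adjusts for T0.

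The Sample size calculation section bases the trial on pain changes in a prior study, requires 22 participants and enrols 26 to allow for 20% attrition.

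**The concern.** Two sources of information on the key outcome have no role in the arm comparison.

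- **The T0 score.** With 13 per arm, chance imbalance in baseline pain can be large. Testing baseline and post-intervention as two separate cross-sections does not correct for it, and the paired tests within each arm do not compare the arms.
- **The pain history of people who leave.** A test on T1 scores can use a person without T1 only if that score is imputed, and no imputation is described. Someone who stops after session 12 has 12 pre-session ratings. The first precedes any treatment, so up to 11 are post-baseline, and the stated test uses none of them. If leaving is related to pain and differs between backward and forward walking, the comparison of those who remain can be biased.

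**Working it through.** **Inputs from the protocol.** 13 per arm; 18 sessions; 22 required and 26 enrolled; 20% attrition; effect size 0.29. The protocol gives no within-person correlation of NPRS scores, so every correlation below is an assumption and is shown over a range.

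**1. The plan's own figures.** 22 × 1.2 = 26.4, which matches the stated 26 (dividing instead, 22/0.8 = 27.5, gives 28). Expected losses are 26 − 22 = 4 on the plan's own margin, or 0.20 × 26 = 5.2 at exactly 20%. The 22 itself is not reproduced by the planned test: if 0.29 is a standardised mean difference, a two-sided independent t-test needs 188 per arm. That is a separate matter and returns only in step 5.

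**2. Gain from adjusting T1 for T0.** The relative variance of the arm difference is 1 − r², where r is the T0–T1 correlation.

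- r = 0.5: 0.75, a 25% reduction.
- r = 0.6: 0.64, a 36% reduction.
- r = 0.7: 0.51, a 49% reduction.

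Estimating the slope costs a little in a small trial. Simulated with 10 to 11 per arm analysed, the reductions were about 20–21%, 32–33% and 45–46%. The gain shrinks if the correlation is weaker: at r = 0.3 it is 1 − 0.91 = 9%.

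**3. What session ratings add for the T1 difference.** The calculation used generalised least squares with a separate mean at each time, known covariance, arms equal at T0, and the rating before session 1 left out. Variances are in squared SD units.

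With no dropout, the T1 t-test has variance 2/13 = 0.1538. Adjusting for T0 gives 0.1154 (exchangeable correlation 0.5) or 0.0785 (0.7). Adding all session ratings leaves both unchanged.

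With 2 dropouts per arm after session 9 (4 in total, the plan's margin), the T1 t-test has variance 2/11 = 0.1818:

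| Assumed correlation | T1 t-test | T1 adjusted for T0 | With session ratings too | Further reduction |
|---|---|---|---|---|
| Exchangeable 0.5 | 0.1818 | 0.1364 | 0.1308 | 4.1% |
| Exchangeable 0.7 | 0.1818 | 0.0927 | 0.0877 | 5.4% |
| Serial, 0.90 per session | 0.1818 | 0.1785 | 0.1756 | 1.6% |
| Serial, 0.95 per session | 0.1818 | 0.1559 | 0.1499 | 3.8% |

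In the serial rows T0 and T1 are 19 steps apart, so their correlation is only 0.90^19 = 0.14 or 0.95^19 = 0.38, and adjustment for T0 gains correspondingly less.

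**4. Where larger gains come from.** Suppose the endpoint were a mean of three ratings instead of T1. Under exchangeable correlation the baseline-adjusted relative variance is r + (1 − r)/3 − r² = 0.42, 0.37 and 0.31 at r = 0.5, 0.6 and 0.7. Step 2 already gives 0.75, 0.64 and 0.51 with no session rating at all. The remainder comes from averaging, which changes the estimand. It also depends on the correlation pattern: under serial correlation ρ the mean of three has relative variance (3 + 4ρ + 2ρ²)/9 = 0.913 at ρ = 0.90 and 0.956 at ρ = 0.95. That is a saving of 9% or 4%, against 33% to 20% under exchangeable correlation of 0.5 to 0.7.

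**5. Effect on power.** At a standardised difference of 0.29 with 13 per arm, power is 11% for the T1 t-test and 13% to 17% for T1 adjusted for T0 at r = 0.5 to 0.7. Averaging all 18 ratings with adjustment, a different estimand, reaches 27% to 32% over exchangeable correlations of 0.3 to 0.7.

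**The case against.** The strongest reply is that the plan is coherent as written. Study design, abstract and Statistical analysis all describe a pre/post trial, and a single end-of-treatment endpoint is a legitimate choice. The protocol never says whether the session ratings are outcome data or monitoring. Chamber pressure is set by pain, so monitoring is a plausible purpose, and leaving monitoring data out of the analysis is no fault. This stands as a defence of T1 as the endpoint. It does not defend leaving T0 out of the arm comparison, nor does it stop ratings already taken from informing the analysis of people without T1.

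A reader might also infer three stronger things that the protocol does not support.

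- **That the analysis is restricted to completers.** No analysis set or missing-data rule is stated, and a full plan not shown may hold one. What can be said is that the stated test, taken alone, needs a T1 score.
- **That session ratings would more than halve the variance.** Reductions of that size combine baseline adjustment with a change of endpoint. For the T1 difference, session ratings add about 0 to 5%.
- **That the session ratings deserve to be primary.** Only the evaluator is blinded, while the Intervention section has the treating therapists report session data. Pain is self-reported, so evaluator blinding protects only partly, but moving to session ratings would weaken even that. A recall period is given for baseline only.

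Finally, a mixed model relies on missing-at-random. If people leave because of pain that earlier ratings do not show, bias remains.

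**Conclusion.** The point holds in a limited form. The stated comparison of arms on pain ignores T0 and, for anyone without T1, ignores all pre-session ratings, in a trial of 26 that expects to lose 4 or 5.

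The quantifiable loss is mainly the missing baseline adjustment: roughly 25 to 50% of the variance at assumed T0–T1 correlations of 0.5 to 0.7, about 20 to 46% once the small sample is allowed for, and less if the correlation is weaker. The gain from session ratings is chiefly protection against selective dropout under an assumption that cannot be verified, with little added precision for the T1 difference.

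The change is worth making, but it does not rescue the trial's power, which stays low at the stated effect size under every scenario computed.

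**What to change.** 1. **Primary analysis.** Keep the evaluator-collected T1 NPRS as the endpoint. Estimate the arm difference at T1 by ANCOVA adjusted for T0 NPRS, with a confidence interval, in place of the unadjusted test.
2. **Supporting analysis, prespecified.** Fit a linear mixed model to weekly means of the pre-session ratings plus T1, adjusted for T0, with arm, week and arm-by-week terms. Name the arm difference at T1 as the contrast. Use a structured covariance, because some 19 unstructured time points cannot be fitted with 26 people, and allow T1 its own variance, since it is a single score rather than a mean. Include every randomised participant with any post-baseline rating. Do not count the rating before session 1 as post-baseline. Exclude ratings taken during walking, because chamber pressure is adjusted to relieve pain at that time.
3. **Wording.** State whether session NPRS is outcome or monitoring data, who records it, and its recall period, which must match T0 and T1 if the ratings are to be modelled together. Align the Study design section with the NPRS section accordingly.

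**Cost.** Item 1 is a change of analysis wording only. Item 2 also needs entry of ratings already planned. The recall period in item 3 is a data-collection change and cannot be applied to ratings already taken. If a final-week or six-week mean is preferred for precision, it should be declared as a different estimand; a six-week mean would dilute an effect that builds up late.
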